***Inclusion Criteria***

1. Confirmed SARS-CoV-2 (COVID-19) infection by a positive test result
2. Either gender
3. Symptomatic for example fever, dry cough, myalgias

***Exclusion Criteria***

1. Confirmed absence of SARS-CoV-2 (COVID-19) infection by a negative test result
2. Have chronic conditions such as heart disease, liver and kidney failure
3. Ongoing respiratory distress or severely dyspneic
4. Pregnant or currently lactating female
5. Immunocompromised, atopic and/or systemic disease(s)
6. On other antiviral drugs
7. History of allergy to any of the drugs to be administered in this study

Both recruitment and administration of study drugs will be carried out by any member of the site investigation team. All site teams have been trained accordingly.

***SPIRIT Guidance:*** *Interventions*

*11a Interventions for each group with enough detail to allow replication, including how and when they will be administered*

Participants will be divided into seven intervention groups (A to G) and eighth group (H) comprising non-consenting individuals observed for supportive care (Figure 1). Study physician(s) will administer three drugs as monotherapy (to three intervention arms), in combination regimen of any of the two trial drugs (to three additional arms), and seventh intervention arm comprising all three drugs. The three drugs with respective dosages are - Hydroxychloroquine Phosphate/Sulfate (200 mg orally 8hr thrice a day for 5 days) versus oseltamivir (75 mg orally twice a day for 5 days) versus Azithromycin (500 mg orally daily on day 1, followed by 250 mg orally twice a day on days 2-5)

***SPIRIT Guidance:***

*11b Criteria for discontinuing or modifying allocated interventions for a given trial participant (eg, drug dose change in response to harms, participant request, or improving/worsening disease)*

Study physicians will observe, interview, and report any suspected adverse drug reaction (sADR) to their unit teams and subsequently to electronic data entry module. “A sADR is an unwanted or harmful reaction experienced following the administration of a drug or combination of drugs under normal conditions of use and is suspected to be related to the drug”. In case of sADR, the participant will be informed of discontinuation of given therapy until resolution of symptoms is observed and/or receipt of corresponding investigations (Electrocardiogram, Hepatotoxicity, Nephrotoxicity, Myelotoxicity) confirm the suspicion or otherwise. Findings will be conveyed to participant and recorded on electronic data module. A written report of any confirmed episode will also be immediately submitted to Drug Regulatory Authority of Pakistan (DRAP) on its prescribed proforma **(attached** as sample). Any decision to modify the study protocol or drug dosage will be informed by aggregated data on ADRs and Drug Regulatory Authority is a statutory forum to exercise these decisions (if warranted) through pre-notified National Data Safety & Monitoring Board (NDSMB). Irrespective of sADR, the study participants reserve the right to withdraw their informed consent at any point of time throughout recruitment period.

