**Abstract**

Objectives

To evaluate the effectiveness of Hydroxychloroquine Phosphate/Sulfate (200 mg orally 8 hourly thrice a day for 5 days) *versus* oseltamivir (75 mg orally twice a day for 5 days) *versus* Azithromycin (500 mg orally daily on day 1, followed by 250 mg orally twice a day on days 2-5) alone and in combination (in all seven groups), in clearing the coronavirus (COVID-19) nucleic acid from throat and nasal swab and in bringing about clinical improvement on day 7 of follow-up (primary outcomes).

Trial Design

An adaptive design, set within a comprehensive cohort study, is chosen because it permits flexibility in this fast-changing clinical and public health scenario. The randomized study will be a multicenter, multiarm, multistage, randomized controlled trial with a parallel design. An observation only cohort will emerge from those not consenting to randomization.

Participants

Eligible will be newly diagnosed patients, either hospitalized or in self-isolation, without any comorbidities or with controlled chronic medical conditions like diabetes mellitus and hypertension. Participants of any gender or age group having tested positive for COVID-19 on Real-Time qRT-PCR (Quantitative Reverse Transcription PCR) will be invited to take part in study at twelve centers across nine cities in Pakistan. Those pregnant or lactating, severely dyspneic or under respiratory distress, already taking a treatment, and with serious co-morbidities like liver or kidney failure will be excluded.

Intervention and Comparator

A total of seven comparator groups will be formed: Each drug (Hydroxychloroquine Phosphate/Sulfate, Oseltamivir and Azithromycin) given as monotherapy (three groups); combinations of each of two drugs (three groups); and a final group on triple drug regimen.

Main Outcomes

The laboratory-based primary outcome will be turning test negative for COVID-19 on qRT-PCR on day 7 of follow-up. The clinical primary outcome will be improvement from baseline of two points on a seven-category ordinal scale on day 7 of follow-up.

Randomization

Participants will be randomized, maintaining concealment of allocation sequence, using a computer-generated random number list of variable block size into multiple intervention groups.

Blinding

Computerized allocation to treatment group will be done upon adding participants demographic details and confirmation of informed consent. Neither physician nor participants will be blinded.

Sample Size

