Secondary outcomes like Quality of Life and Symptoms Score will be recorded on day 0 and 7 using standardized tools such as World Health Organization Quality of Life Questionnaire (WHO QoL) and Wisconsin Upper Respiratory Symptoms Survey (WURSS) respectively (copies **attached)**. The former is expected to capture participant’s lived experience during care that has not been documented in literature to date. The latter is expected to indicate any respiratory co-infection including those acquired from the hospital. The investigators will also monitor and record variables including duration it takes to oxygenate and ventilate, duration stayed oxygenated and ventilate, number of hospitals stay days, admission to intensive care, and mortality. This methodology has been peer reviewed by an external expert **(see annex 1).** A GCP certified, experienced researcher will conduct the training of up to 50 investigators across 13 participating sites to prepare them for all aspects of this study.

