***SPIRIT Guidance: Harms***

*22 Plans for collecting, assessing, reporting, and managing solicited and spontaneously reported adverse events and other unintended effects of trial interventions or trial conduct*

Diagnostics such as Electrocardiogram, Hepatotoxicity, Nephrotoxicity, Myelotoxicity are indicated once ADR is suspected and explained on Page 8 (Methods). Any additional incident or finding defined as adverse event (AE) during recruitment period will be reported to IT module. An adverse event (AE) is “any untoward medical occurrence in a patient or clinical investigation subject administered a pharmaceutical product that does NOT necessarily have a causal relationship with this treatment. For example, a physical injury resulting from fall or slip, a natural calamity during in-patient stay etc”. Investigators are also trained to ensure safe and secure environment for participants to provide necessary psychosocial support, when indicated.

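### In an open-label trial, the regulator report waits for a confirmed reaction and the data named for protocol or dosage decisions are physician-attributed ADRs; no route is stated for deaths and all-cause adverse events

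*Protocol*

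**What the plan says.** Item 11b (discontinuing or modifying interventions) sets out the safety process. Detection lies with the treating team: "Study physicians will observe, interview, and report any suspected adverse drug reaction (sADR) to their unit teams". The definition there requires that the reaction "is suspected to be related to the drug". The Abstract, under Blinding, says: "Neither physician nor participants will be blinded".

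Item 11b then fixes two rules:

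- The regulator report: "A written report of any confirmed episode will also be immediately submitted to Drug Regulatory Authority of Pakistan".
- The evidence for change: "Any decision to modify the study protocol or drug dosage will be informed by aggregated data on ADRs". DRAP takes these decisions through the NDSMB.

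Other events are handled elsewhere. Item 22 (Harms) defines an adverse event without requiring a causal link and has it entered in the IT module. Its illustration reads: "For example, a physical injury resulting from fall or slip, a natural calamity during in-patient stay". Item 12 (Outcomes) lists among the recorded variables "admission to intensive care, and mortality".

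Items 21a, 21b and 23 give the NDSMB power to scrutinise data, halt the study or an arm, hold closed sessions and meet at any time. Item 25 gives an open-ended list of reasons for changing the protocol, NDSMB review among them.

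**The concern.** COVID-19 and the study drugs can produce similar events, so a physician judging one patient often cannot tell illness from drug harm. An excess of harm in an arm shows reliably only when all events are compared across randomised arms, whatever their presumed cause. The sentence in item 11b that names the evidence for changing the protocol or dosage names a different quantity: events that an unblinded physician has already attributed to a drug.

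That attribution may differ by arm. The Introduction mentions earlier cardiotoxicity concerns about hydroxychloroquine, and the seven arms carry one, two or three drugs. Physicians may be readier to suspect the drug in some arms than in others, which would distort ADR totals in either direction.

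The reporting trigger raises a second problem. If a report waits for confirmation, the episodes hardest to investigate, including sudden deaths, are the ones that may not produce one. The Abstract's trial status describes recruitment as continuing, so these rules govern the safety of people still being enrolled.

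**Working it through.** No figure in the Protocol bears on this point, so the check is a comparison of sections plus one line of algebra.

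**Step 1. Follow three kinds of event through the text.**

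| Event | Written report to DRAP (item 11b) | In the data named for modification decisions (item 11b) | Recorded |
|---|---|---|---|
| Suspected reaction, confirmed | Yes | Yes | Yes |
| Suspected reaction, cannot be confirmed | Not required | Unclear: the text moves from suspected ADRs to ADRs without saying whether unconfirmed ones count | Yes |
| Death, intensive-care admission or other event attributed to COVID-19 | Not required | Not named | Yes (items 12 and 22) |

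The second row can realistically occur. Item 11b links confirmation to cardiac, liver, kidney and marrow investigations. Item 15 (Recruitment) allows participants to be treated at home, with clinical data other than swabs taken by phone when they cannot travel. Item 12 says that diagnostic facilities vary between sites. If someone dies suddenly at home, such investigations may never be done.

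**Step 2. Look for a stated route from the record to the decision.** Item 22 ends at the IT module. Items 21a, 21b and 23 give the NDSMB authority to act but do not list what it receives. The interim content that is described consists of sample size, time to clearance and dropping less promising arms (item 14), and baseline co-morbidity imbalance (item 20, which adds that groups are not disclosed). None of these mentions deaths or adverse events. No section sets a reporting rule for serious events or deaths that applies regardless of attribution.

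**Step 3. What attribution does to a count.** Let e1 and e2 be the true rates of one kind of event in two arms, and s1 and s2 the probabilities that a physician attributes such an event to the drug. Then:

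- ratio of ADR rates = (e1 × s1) / (e2 × s2) = (e1/e2) × (s1/s2)
- ratio of all-event rates = e1/e2

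The ADR ratio equals the true ratio only if s1 = s2, and open-label attribution gives no assurance of that. The all-event ratio does not contain s. This matters to the extent that ADR totals are compared between arms; item 11b says they are aggregated but does not say how.

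**The case against.** A reader might infer that only ADR totals count and that deaths attributed to COVID-19 never enter a safety decision. The document does not support that reading:

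- Item 11b says decisions are informed by ADR data. It does not say by nothing else, and item 25 lists further grounds without closing the list.
- The NDSMB's remit in item 21a is data in general. Its power to halt an arm is not tied to ADR counts, and items 21b and 23 add closed sessions, termination decisions and review at any time.
- Deaths and intensive-care admissions are recorded whatever the attribution, and nothing withholds them from the board.
- The adverse-event definition in item 22 already covers any cause. The fall and the calamity are only examples, so a deterioration thought due to COVID-19 already fits.

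It is also fair to say that item 11b does not state how a fatal episode without investigations is classified. The DRAP form and the board's notification are attachments not shown, and by-arm safety tables are often left to an analysis plan or board charter.

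All of this stands against the broad reading. It does not remove the narrower point. Item 11b is not silent: it states a reporting trigger and names the evidence, and both depend on attribution or confirmation. Authority to look at data is not a statement that all-cause events by arm will be supplied.

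**Conclusion.** The point holds in limited form. The stated trigger for the DRAP report is confirmation. The only data that item 11b names for protocol or dosage decisions depend on the judgement of unblinded physicians. Deaths, intensive-care admissions and all-cause adverse events are collected, and the board may act on them, but they are not named as an input and their route to the board or DRAP is not written down.

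No size can be given. The document states neither an event rate for this population nor how often physicians would attribute events to a drug. The global fatality figure of 3 – 4% in the Introduction does not supply one, because item 10 excludes people with respiratory distress, severe dyspnoea or liver and kidney failure. Nor would a count of expected deaths measure the defect, since the board is free to consider deaths.

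The conclusion assumes that the attachments not shown do not already state the missing route. If they do, item 11b should refer to it. This is an inexpensive improvement to safety oversight; it does not show that deaths are being disregarded.

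**What to change.** 1. In item 11b, replace the reference to aggregated ADR data with: *all adverse events, ICU admissions and deaths by randomised arm regardless of causality, together with ADRs, supplied to the NDSMB closed session*. Coded arm labels would keep this consistent with the item 20 statement that groups are not disclosed.
2. In item 11b, make the DRAP report of a fatal or otherwise serious event depend on suspicion, with confirmatory results sent as follow-up.
3. Reconcile items 11b, 21a, 22 and 25 so that they agree on which data inform modification and halting, and state the route from the IT module to the NDSMB and DRAP.
4. Optionally, add clinical or laboratory examples to the adverse-event text in item 22. The definition already covers them.

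The cost is mainly wording. The events are already recorded, so no new data are collected. The downside is more expedited reports and one more table for the board. No dose or treatment rule changes.

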***SPIRIT Guidance:***

*11c Strategies to improve adherence to intervention protocols, and any procedures for monitoring adherence (eg, drug tablet return, laboratory tests)*

Administration of drugs to participants will be directly observed by the clinical staff at the study sites. Each of the site team has been trained to maintain a record of pharmaceutical supplies from stock entries to disposition. All supplies are labelled NOT FOR SALE from the source. The site teams will be responsible to project demand corresponding with the rate of recruitment, monitor appropriate usage, and maintain a folder of used drug packaging for site audits.

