***Methods: Participants, interventions, and outcomes***

**4 PARTICIPANTS**

***SPIRIT Guidance: Study setting***

*9 Description of study settings (eg, community clinic, academic hospital) and list of countries where data will be collected. Reference to where list of study sites can be obtained*

Study sites comprise major public-sector tertiary care health facilities and Covid-19 field hospitals being setup within province of Punjab. Hospitals in other provinces and federal areas will also be invited for participation. Households with self-isolating individuals could also participate in the study. A list of hospitals with confirmed participation has been attached as **Annex 3.**

***SPIRIT Guidance:*** *Eligibility criteria*

*10 Inclusion and exclusion criteria for participants. If applicable, eligibility criteria for study centers and individuals who will perform the interventions (eg, surgeons, psychotherapists)*

Eligible will be newly diagnosed patients without any comorbidities or those with controlled chronic medical conditions, e.g. diabetes mellitus and hypertension. Participants of either gender or age group having tested positive for COVID-19 on qRT-PCR (Quantitative Reverse Transcription PCR) will be invited to take part. Participants who are pregnant or lactating, are already taking any treatment, under respiratory distress or severely dyspneic, have liver and kidney failure will be excluded from the study. Each participant will undergo baseline investigation i.e., liver function tests, renal function tests, urinalysis, and Complete Blood Count; at the time of enrollment. However, diagnostic facilities and hospital admission criteria could vary across cities. A case report form (CRF) has been developed for this proposal and **attached** at the end of this document.

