***SPIRIT Guidance: Recruitment***

*15 Strategies for achieving adequate participant enrolment to reach target sample size*

All patients fulfilling the eligibility criteria and providing informed consent are eligible for this study. Going by the projections, it is expected to enroll substantial number of participants from clinical facilities. A coordination group has been created on digital platform for immediate response to queries, learning from each other’s experiences, and continuity of operations. However, if health system indicates creep, investigators could recruit patients self-isolating at homes. Upon identification by site investigators in the hospital, this cohort would be contacted by trained researchers and data collectors via phone and if informed consent is obtained, recruited. The allocated treatment medicines for 14 days would be delivered. Similarly, swab samples and other clinical information would be collected from participants’ homes in case they cannot travel for testing. All other clinical data would be collected via phone and entered directly into the IT module. The unused or used drug packaging will be collected from participants’ homes upon completion of recruitment period of testing negative on PCR whichever comes first. It is expected that a wider pool of both hospitalized and home-isolated patients would be enough to meet the estimated sample size within the given timeframe.

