***SPIRIT Guidance: Implementation***

*16c Who will generate the allocation sequence, who will enrol participants, and who will assign participants to interventions*

Randomization sequence was created using Sealed Envelope Ltd 2019 and was stratified by study center and age using random block sizes of 28 and 42 sizes into seven treatments (11). Before randomizing, recruiting physician will confirm eligibility and obtain written informed consent from the participant. Upon entering participant’s demographic details in the IT module, a unique patient ID for the said center and treatment arm would be allocated automatically meaning the recruiting physician has no control over assigning intervention.

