***SPIRIT Guidance: Statistical methods***

*20a Statistical methods for analyzing primary and secondary outcomes. Reference to where other details of the statistical analysis plan can be found, if not in the protocol*

*20b Methods for any additional analyses (eg, subgroup and adjusted analyses)*

*20c Definition of analysis population relating to protocol non-adherence (eg, as randomized analysis), and any statistical methods to handle missing data (eg, multiple imputation)*

All trial data will be analyzed by biostatistician based at the University of Health Sciences, Lahore, using an a priori, approved analysis plan (SPSS 25.0). Interim analyses at each stage (first stage will be 10% of the total sample size) of the adaptive design will be pre-planned and undertaken confidentially keeping investigators and participants blind till the end of the trial. Primary and secondary outcomes will be analyzed in accordance to the group in which the participants were randomized deploying the intention-to-treat principle. The primary analysis will be expressed as odds ratio (OR) of the comparison between groups for the primary outcome. Interim analyses will be conducted without disclosing groups, thereby maintaining a level of blinding in interpretation of interim results. The confidential interim analyses at each stage of the adaptive design will examine for imbalance in co-morbidity at baseline. If any differences are observed then stratification may be modified confidentially. The results will be reported as point estimates and 95% confidence intervals. Secondary analysis will include in time-to-event data to directly compare the data among groups with survival plots and hazard ratios. This will permit evaluation of the decision to continue beyond Day 7 of treatment upon testing negative, potential drug effects besides informing valuable understanding of drug effectiveness. Stratified analyses will be done by baseline COVID-19 positive status upon testing and age groups. Multiple regression and Cox proportional hazards stratified analysis will be used to adjust for a small number of covariates taken from stratification factors if there were baseline imbalances. Secondary analyses will deploy multiple regression models as well Chi square, Fisher’s exact test and one-way ANOVA to compare groups. The two-sided p-value less than or equal to 0.05 will be taken as significant. Imputation method will be used to handle missing data.

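### Home participants have no stated record of doses during treatment, and care setting is left out of both stratification and the covariate rule

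*Protocol*

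**What the plan says.** **Drug administration.** Item 11c of the protocol (adherence) states: "Administration of drugs to participants will be directly observed by the clinical staff at the study sites". The closing paragraph of the Exclusion Criteria adds: "Both recruitment and administration of study drugs will be carried out by any member of the site investigation team".

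**Where participants are.** Under Study setting (item 9): "Study sites comprise major public-sector tertiary care health facilities and Covid-19 field hospitals being setup within province of Punjab". The same paragraph continues: "Households with self-isolating individuals could also participate in the study". The Abstract names both settings without condition: "Eligible will be newly diagnosed patients, either hospitalized or in self-isolation, without any comorbidities".

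**How home participants are handled.** Recruitment (item 15) makes home enrolment an option if the health system comes under strain. These patients are identified by hospital investigators, contacted by phone and sent their medicines. Swabs are taken at home if they cannot travel. For the rest: "All other clinical data would be collected via phone and entered directly into the IT module". Their drug packaging is retrieved later.

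**Allocation and adjustment.** Under Implementation (item 16c), the sequence "was stratified by study center and age using random block sizes of 28 and 42 sizes into seven treatments". Under Statistical methods (item 20), regression and Cox models are to "adjust for a small number of covariates taken from stratification factors", and this is conditional on imbalance being found at baseline. The stratified analyses listed there use baseline COVID-19 test status and age.

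**The concern.** There are two linked gaps.

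First, the adherence procedure was written for patients on a ward. For patients at home the protocol describes delivery, phone contact and later collection of packs, but nothing that records doses as they are taken. Packs collected later cannot show when the first dose was taken or whether doses were on schedule. With a day-7 primary endpoint, both matter.

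Second, hospital and home patients plausibly differ in prognosis, and the clinical primary outcome (a two-point improvement on a seven-category scale) is obtained differently in each group, in a trial where neither physicians nor participants are blinded. A variable of this kind, known at enrolment, is a natural covariate. The stated rule excludes it, because covariates come from the stratification factors and are used only after imbalance is seen.

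At stake are the precision of the day-7 comparisons, some exposure to chance imbalance, and the ability to tell an ineffective regimen from one that was not taken.

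**Working it through.** **1. The protocol's own figure.** Inputs from Sample size (item 14): 50% v 60% negative at day 7, 5% significance, 90% power, about 520 per group. Item 20 makes the test two-sided.

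n = [1.96 × √(2 × 0.55 × 0.45) + 1.2816 × √(0.25 + 0.24)]² / 0.10² = (1.379 + 0.897)² / 0.01, which rounds up to 519. Power at 520 per group is 90.1%. The figure reproduces and is not disputed.

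**2. The adherence text side by side.**

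| Feature | On-site participants | Home participants |
|---|---|---|
| Who gives the drug | Site team | Not stated; a supply is delivered |
| Observation of dosing | Direct, by clinical staff | None described |
| Check after dosing | Packaging folder for audit | Packaging collected later |
| Clinical data | Collected at the site | By phone |

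That home doses go unobserved is an inference from delivery plus phone follow-up; the protocol does not say so in words. Item 15 also refers to a 14-day supply while the regimens in the Objectives run 5 days. These must be reconciled too, because a pack count needs a fixed number of expected doses.

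**3. Where care setting could enter.** Stratification: centre and age only. Covariates: from the stratification factors, if imbalanced. Stratified analyses: test status and age. Interim change of stratification: for co-morbidity imbalance only. Setting appears in none of these. Home patients are identified through hospitals, so one centre can hold both settings, and centre is only a partial proxy.

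**4. Size of dilution, by assumption.** Let h be the home share and c the share of home patients who take treatment. The protocol gives neither. Assume c is the same in both arms, taking treatment is all-or-nothing, and the lower rate stays at 50%. The intention-to-treat difference is then 10 × [1 − h(1 − c)] points.

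| h | c | Difference (points) | Power at 520 | n per group for 90% |
|---|---|---|---|---|
| 10% | 90% | 9.9 | 89.5% | 529 |
| 25% | 80% | 9.5 | 86.9% | 575 |
| 50% | 80% | 9.0 | 83.1% | 642 |
| 50% | 60% | 8.0 | 73.6% | 814 |
| 75% | 60% | 7.0 | 61.9% | 1065 |

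**5. Size of chance imbalance.** Ignoring any help from centre and age stratification, the standard deviation of the between-arm difference in home share is √(2h(1 − h)/n).

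- At n = 520: 1.9 points for h = 10%, 2.7 for 25%, 3.1 for 50%.
- At n = 67 (470 / 7, if all those recruited by July 2020 had been randomised): 5.2, 7.5 and 8.6 points.

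If setting moved the response rate by 10 points (an assumption, borrowed from the planned treatment difference), a one-standard-deviation imbalance at h = 50% would shift a comparison by 0.031 × 10 = 0.3 points at 520 per arm and 0.086 × 10 = 0.9 points at 67 per arm.

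**The case against.** The strongest reply is that the text is looser than it is wrong. Item 11c speaks of observation at the study sites, and item 9 defines sites as hospitals and field hospitals, with households named separately. Read that way, the statement never covered home patients. This stands in part: a reader might infer a flat contradiction, and the wording does not compel one. The administration sentence under the Exclusion Criteria has no such limit, however, and on the narrower reading nothing is left that records home doses during treatment.

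Packaging retrieval is also an adherence check of a kind, so it would be wrong to say that home patients have none. It is weak and comes late.

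On covariates, item 20 mentions multiple regression elsewhere without listing variables and refers to an approved analysis plan that is not at hand. The case report form is not shown either, so one cannot say that setting goes unrecorded. That stands. What the protocol does state is still a restrictive rule that depends on observed imbalance, and a plan that followed it would omit setting.

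A reader might infer that arms will differ systematically by setting. Randomisation balances setting in expectation, so the documents do not support that. Nor can it be shown how the scale behaves by setting, because its categories are not defined in the text at hand.

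Finally, the power figures rest on assumed inputs, home recruitment is conditional in item 15, and item 14 calls 520 indicative and plans re-estimation to hold 90% power. All of this is fair. One limit applies: a re-estimation that is truly blinded sees only the pooled rate, which would move from 55% to 53.5% even in the worst row above, so it would not readily reveal dilution.

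**Conclusion.** The point holds as two modest defects in stated rules. The administration and adherence statements do not fit the home participants whom the recruitment section admits, and no adherence record during dosing is stated for them. Care setting is outside the stratification factors and therefore outside the adjustment rule.

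The consequence is lost precision, possible chance imbalance (small at 520 per arm, larger at early stages) and a null result that is harder to interpret. It is not bias between arms. Nor is a null result uninterpretable, since on-site dosing is observed and home packs are retrieved.

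No single figure for lost power can be claimed. Over the assumed range, power at 520 per group goes from about 89.5%, which is negligible loss, to about 62%. The range assumes equal, all-or-nothing non-adherence in both arms. If patients at home on several drugs omit more doses than those on one, the formula no longer applies. Recording doses and adjusting for setting would not restore this power under intention to treat; they would make the result easier to read and the comparison more efficient.

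**What to change.** - Limit the direct-observation statement in item 11c, and the administration sentence under the Exclusion Criteria, to on-site participants. Reconcile both with item 15.
- For home participants, record the date of first dose and the doses taken of each allocated drug at the day 3, 5 and 7 assessments already scheduled under Outcomes (item 12). Keep packaging collection as a cross-check.
- Record care setting (hospital or home) at randomisation. For those already enrolled, take it from site files.
- Replace the imbalance-triggered rule in item 20: prespecify care setting, together with the stratification factors, as a covariate for both day-7 primary outcomes regardless of observed imbalance. State that the adjusted odds ratio is primary, because in a logistic model it is not the same quantity as the unadjusted one.
- Give results by setting as descriptive only. Seven arms, two primary outcomes and two settings would otherwise add many small contrasts tested at 0.05.

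The cost is protocol wording, a few data fields and one more model term, with no new visits. The downside is that home dose counts are self-reported.
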